## Methods and design

Visual-acoustic Intervention with Service delivery In-person and via Telepractice (VISIT) is a parallel-group prospective randomized controlled non-inferiority trial measuring the efficacy of visual-acoustic biofeedback intervention for RSSD affecting /ɹ/ when delivered online versus in-person. All participants will receive visual-acoustic biofeedback intervention following a standard protocol and schedule; they will be randomly assigned to receive this intervention either in the laboratory setting or via online telepractice. Participant allocation in each group will be stratified by pre-treatment severity, since previous research has identified this variable as an important indicator of subsequent treatment response. Finally, allocation will additionally be stratified by site (Montclair, New Jersey; Syracuse, New York). Although not all participants will be physically present at their allocated site during treatment delivery, they must reside close enough to their study site to be able to participate in-person if randomized to that condition. They will also interact with a site-specific study team, which could potentially be relevant for study outcomes.

We plan to enroll a total of 76 children with RSSD. The power analysis to determine this sample size was based on a comparison of 12 participants from a previous study who received visual-acoustic biofeedback treatment in the in-person setting and 11 participants who received a comparable duration of visual-acoustic biofeedback treatment via telepractice. The participants seen in person had an average change score of 39.8% points (standard deviation = 25.8% points) and the participants seen online had an average change score of 36.8% points (standard deviation = 22.6% points). The population standard deviation of the outcome, after controlling for effects of clinician and baseline accuracy, was estimated at 18% points. Using the formula from Flight & Julious 2016 [32], the sample size of 38 participants per group was computed to achieve 80% power for an alpha level of 5%, assuming the non-inferiority margin delta derived as described under *Data analysis plan*. Power analysis was conducted using an online power calculator for non-inferiority trials [33].

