### Group allocation

Participants will be randomly allocated to one of two groups in a 1:1 ratio. The *in-person* group will receive visual-acoustic biofeedback treatment from a clinician in a private room in research space at Syracuse University or Montclair State University, while the *telepractice* group will receive equivalent treatment delivered via videoconferencing. As indicated above, random allocation will be stratified by both baseline accuracy and study site. To determine baseline accuracy, the stimulability probe will be rated by the clinician who administered the evaluation and a clinician at the other study site. Based on these ratings, participants will be categorized as more stimulable (both clinicians score the participant as showing > 0% accuracy in baseline stimulability probe) or less stimulable (at least one clinician scores 0% accuracy in baseline stimulability probe). The study statistician will generate confidential participant treatment assignments in batches, where each batch corresponds to a combination of site (Montclair State University versus Syracuse University) and response category (more versus less stimulable). Within each batch, half of the participants in each of the four combinations of accuracy level and site will be allocated to the in-person condition and half allocated to the online condition. To avoid a situation where study team members can predict the allocation of an upcoming participant based on their knowledge of previous allocations within the batch, batch sizes were randomly chosen from a collection of possible sizes ranging from 16 to 96 (reflecting the fact that the size of each batch needs to be a multiple of eight).

In cases where a participant drops out prior to study completion, we will invite the participant to return for a follow-up assessment after the typical duration of treatment elapses, in order to measure their outcomes in the absence of the treatment. For participants who decline to participate in this follow-up assessment, in the intention-to-treat analysis, we will generate an imputed score based on data from the other participants in the group the missing participant was assigned to. To support this imputation, participants will complete one assessment session at the midpoint of treatment (after treatment session 10). We will also conduct an adjusted per-protocol analysis, described below under *Data analysis*.

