### Data analysis plan

The first statistical consideration for this study is the value of the margin delta (Δ), which represents the maximum acceptable loss of effect for an alternative treatment relative to an established one in a non-inferiority trial. Previous literature has suggested that delta may be defined as “less than the minimum difference of clinical interest (i.e., the minimum clinically important difference; MCID)” [28, 57]. We defined the MCID with reference to a meta-analysis of eleven single-case experimental studies of biofeedback intervention for RSSD previously published by our team [58]. In this meta-analysis, we generated de-identified plots of participants’ accuracy before and after treatment, based on perceptual ratings aggregated over blinded listeners. Three experienced researchers visually inspected these plots and reached a consensus judgment classifying each participant as responding or failing to respond to treatment. This “gold standard” binary classification was then used to compute sensitivity, specificity, and combined sensitivity-specificity for various cutoff values. ROC curve analysis revealed that a raw mean difference of 13.9% points represented the optimal cutoff between responder and non-responder categories (optimal combined sensitivity-specificity using Youden’s J). We adopt this cutoff value as the MCID. However, it is recommended that Δ be set to a value less than the MCID. Previous non-inferiority trials in the speech context have considered different values, including half of the MCID [27] or 75% of the MCID [28]. Based on the argument that high variability in response to speech treatment may lead to large confidence intervals [28], we will set our value of delta to 75% of the MCID, or 10.4% points.

The primary statistical model described below will be fit twice, once following the intention-to-treat principle, with imputed scores generated for cases of attrition, and once in an adjusted per-protocol analysis; see below for additional detail. Assessment of outcomes following both approaches is recommended for non-inferiority trials [25]. If the lower bound of the 95% confidence interval centered on the observed difference falls above the noninferiority margin of -10.4 in both models, we will conclude that noninferiority has been established.

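### The sample size matches a one-sided 5% test, but non-inferiority is judged by a 95% confidence interval (one-sided 2.5%), so 38 per group gives about 70% power, not 80%

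*Protocol article*

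**What the plan says.** All quantities that fix the primary test appear in the protocol article.

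- **Size and power** (Methods and design): "We plan to enroll a total of 76 children with RSSD", and "the sample size of 38 participants per group was computed to achieve 80% power for an alpha level of 5" per cent. Whether the 5% is one-sided or two-sided is not stated.
- **Variability** (same section): the SD of the outcome, "after controlling for effects of clinician and baseline accuracy, was estimated at 18% points".
- **Margin** (Data analysis plan): "we will set our value of delta to 75% of the MCID, or 10.4% points".
- **Allocation** (Group allocation): "Participants will be randomly allocated to one of two groups in a 1:1 ratio".
- **Decision rule** (Data analysis plan): "If the lower bound of the 95% confidence interval centered on the observed difference falls above the noninferiority margin of -10.4 in both models", non-inferiority is concluded. The description of the linear model in the same section again specifies a 95% interval for the group difference in change scores.

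The article nowhere mentions a 90% interval or a one-sided 95% bound.

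**The concern.** A two-sided 95% interval leaves 2.5% in each tail. Requiring its lower limit to clear the margin is therefore a one-sided test at 2.5%. If the sample size was computed for a one-sided 5% test, it belongs to a less demanding test than the one that will decide the trial, and the stated power does not apply.

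What is at stake is the chance of an inconclusive trial. If telepractice and in-person delivery are truly equal, the planned 20% risk of failing to show non-inferiority is understated, and such a failure could be misread as telepractice losing efficacy. Leaving the two alphas unreconciled also leaves room for argument, once results are known, over whether a 90% interval had been meant.

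**Working it through.** **Inputs.** SD 18, 80% power, 38 per group and alpha 5% come from Methods and design. Margin 10.4 and the 95% interval come from the Data analysis plan. The true difference used for sizing is not stated, so 0 is tried first.

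**Formula.** n per group = 2 × SD² × (z_α + z_β)² / (margin − true deficit)², with z_β = 0.8416 for 80% power.

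**Step 1: reproduce the plan's figure.** One-sided 5%, z_α = 1.645:

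2 × 18² × (1.645 + 0.8416)² / 10.4² = 648 × 6.183 / 108.16 = 37.04, rounded up to **38**. An exact t calculation also gives 38.

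**Step 2: apply the planned rule.** One-sided 2.5%, z_α = 1.960:

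648 × 7.849 / 108.16 = 47.02, rounded up to **48** (49 by the t calculation).

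**Step 3: power at 38 per group, true difference 0.**

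SE = 18 × √(2/38) = 4.13, and 10.4 / 4.13 = 2.518.

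| Test | Normal | Noncentral t, 71 df |
|---|---|---|
| One-sided 5% (90% interval) | Φ(2.518 − 1.645) = 80.9% | 80.2% |
| One-sided 2.5% (95% interval, as planned) | Φ(2.518 − 1.960) = 71.2% | 70.0% |

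The 71 df are 76 minus five coefficients: intercept, group, site, stimulability stratum and baseline accuracy.

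**Step 4: interval width.** The expected half-width is 1.994 × 4.13 = 8.2 points for the 95% interval, against 1.667 × 4.13 = 6.9 for the 90% interval that 38 per group implies.

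**Step 5: do other readings rescue the 80%?**

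- *The 5% is two-sided.* The requirement is then 48 or 49, and 38 is too small.
- *The earlier data's difference was assumed.* That difference is 39.8 − 36.8 = 3.0 points. The requirement is 74 per group at one-sided 5% and 93 at one-sided 2.5%. Power at 38 under the 95% rule is Φ(7.4/4.13 − 1.960) = 43% (42% by t).
- *The raw SDs of 22.6 to 25.8 were used.* With true difference 0 and one-sided 5%, the requirement is 59 to 77 per group.
- *The margin was not rounded* (0.75 × 13.9 = 10.425). Power at 38 under the 95% rule is 71.4% (normal) or about 70% (t).
- *A smaller SD applies.* For 38 per group to give 80% under the 95% rule, the SD would have to be 10.4 / (2.802 × √(2/38)) = 16.2. The article gives no such value.

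Of these readings, only one-sided 5% with SD 18 and true difference 0 returns the planned 38.

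**The case against.** The strongest reply has three parts.

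First, the article never calls the 5% one-sided and never states the assumed true difference. Both are inferred from the fact that together they return 38, and the cited formula and online calculator cannot be inspected here. That is correct and should be said openly. It does not save the stated power, because the alternative readings tried require more than 38 per group.

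Second, the mismatch is in the conservative direction. The 95% rule is clear, prespecified and stricter than the sizing implies. It does not raise the risk of falsely declaring non-inferiority, and it biases neither the estimate nor the interval. This stands, and it limits the harm to overstated power. The sizing arithmetic is also correct for the test it matches; the fault is that this is not the test that will be used. Nor does the article equate failure to show non-inferiority with inferiority, so the risk of misreading lies with later readers.

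Third, covariate adjustment might recover some power. But the SD of 18 is already an adjusted figure, reduced from raw SDs of 22.6 and 25.8, so that gain has been spent.

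A full protocol or analysis plan may say more. Here, however, the article itself states the alpha, the power, the sample size and the decision rule, and they do not agree.

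**Conclusion.** The concern holds. Under the plan's own SD and margin, with a true difference of zero, 38 per group gives about 70% power for the stated 95% interval rule, against the 80% claimed. The type II error is about 30% instead of 20%, half as large again as planned. To reach 80% under that rule takes 48 to 49 per group, or 96 to 98 in total instead of 76.

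The conclusion rests on reading an interval centred on the estimate as two-sided, which is the natural reading, and on the inferred zero difference. About 70% is a best case. It assumes complete data and a single analysis, whereas both the intention-to-treat and the adjusted per-protocol models must clear the margin, and the article states no allowance for dropout in the 76. With the 3-point telepractice deficit seen in the earlier data, power would be about 42 to 43%.

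**What to change.** Keep the 95% interval rule and correct the power paragraph in Methods and design. Suggested wording: *Non-inferiority is tested at a one-sided alpha of 2.5% (lower limit of the two-sided 95% confidence interval). With 38 participants per group, an SD of 18 points and a true difference of 0, power is about 70% for a single analysis with complete data.* This costs one sentence in the protocol, and in the registration if it carries the same claim. The stated power becomes less favourable, and no participants are added.

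Two alternatives exist:

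- **Resize.** Raising the total to 96 to 98 is what delivers the stated 80% under the stated rule with the plan's own SD and margin. It costs 20 to 22 more children, before any allowance for dropout.
- **Declare a one-sided 5% test.** If that was the real intention, say so, justify it, and rewrite the rule in the Data analysis plan with a 90% interval before any outcome is rated. This doubles the one-sided error from 2.5% to 5% relative to the published rule, and enrolment began in August 2024, so the change would need an open explanation.

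Whichever is chosen, the power paragraph and the decision rule should state the same one-sided alpha.

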### Recruitment

This study received ethics approval through the Biomedical Research Association of New York (BRANY, protocol #18-10-393). VISIT is a multi-site study with two sites coordinating treatment (Montclair State University and Syracuse University) and a central site responsible for data processing/analysis (New York University). Written assent and permission will be obtained from all study participants and their parent or guardian. REDCap electronic data capture tools [34, 35] hosted at Syracuse University will be used to obtain electronic consent/assent and responses to questionnaires; it will also be used for entry of study data, including scores on eligibility testing and treatment session information. Double-entry and range-restricted data fields will be used for quality control.

Participants will be recruited primarily through referrals from community SLPs, who will be contacted by informational posts to listservs, social media channels, alumni lists, and personal contacts. Other participants may be referred directly by their parent/guardian, who will be contacted through announcements posted in parenting groups on listservs and social media, as well as through flyers displayed in public places such as libraries, schools, and pediatricians’ offices. Participant enrollment began in August 2024.

### Eligibility criteria

All participants must be aged between 9;0 and 17;11 (years; months) at the time of enrollment. Participants must speak English as a dominant or equally dominant language and are required to have begun learning English by age 3, as indicated by parent report. In addition, parent report must indicate that participants hear a rhotic dialect of English (i.e., a dialect of English in which the /ɹ/ sound is pronounced in syllable-final position, such as Mainstream American English in contrast with British Received Pronunciation) from at least one speaker in the home, and that participants have expressed a desire to change the way they pronounce the /ɹ/ sound. Participants must have no history of sensorineural hearing loss or developmental disability (e.g., cerebral palsy, Down Syndrome), per parent report. Additional exclusionary criteria include: history of major brain injury, brain surgery, or stroke in the past year; diagnosis of epilepsy or other neurological disorder with seizure incidents or medication changes in the past six months; or the presence of orthodontia that crosses the palate, such as a palate expander.

Participating families will also be required to meet minimum technology requirements in the home, in the event the participant is randomized to receive treatment via online telepractice. Specifically, participating families must report having access to a laptop or desktop computer, not a tablet or Chromebook, and they must report having a broadband internet connection in the home. In addition, participating families must attest that there is a quiet space in the home for the child to join online study sessions.

During the in-person evaluation session, participants must pass a brief examination of oral structure and function and a pure-tone hearing screening at 20 dB Hearing Level. To rule out language deficits that could interfere with participants’ response to intervention, all participants are required to exhibit language skills broadly within normal limits. This will be established either by a passing score on the Clinical Evaluation of Language Fundamentals-5 (CELF-5) [36] screening measure or by a standard score of at least 80 on the Core Language Index of the CELF-5. Additionally, to limit heterogeneity in participants’ level of severity at baseline, participants are required to score below 30% correct (based on the average across two trained listeners) on a 24-item probe list eliciting /ɹ/ at the word level across a balanced representation of phonetic contexts. The Goldman-Fristoe Test of Articulation-3 (GFTA-3) [37] will be administered for descriptive characterization of participants but will not be used as a criterion for inclusion.

As described in our previous research [15], we will use the Syllable Repetition task [38] and the multisyllabic word task of the LinguiSystems Articulation Test [39] to rule out childhood apraxia of speech (CAS) in participants. Participants who score above the predetermined cutoff representing likely CAS on both tasks will be excluded. Participants who score above the cutoff on only one of these two measures will be administered a maximum performance task as a tiebreaker measure. Participants whose task performance is consistent with signs of CAS as outlined by Thoonen et al. [38–41] will be excluded; participants who score within normal limits will be included.

Both male and female children will be recruited for this study, and no participants will be excluded based on sex/gender or racial/ethnic group. In light of the general population demographics of children with speech sound disorders [4], however, we expect that more males will be referred than females.

### Assessment process

An online screening instrument and follow-up phone call will be used to identify any exclusionary criteria that can be indicated via parent report, such as being outside the age range or having a diagnosis of developmental disability. This call will also provide a detailed description of the study and its requirements, including minimum technology needs and scheduling expectations. Families who pass the phone screening will be invited to participate in an in-person eligibility assessment, 1–2 h in duration. Prior to the eligibility visit, consent and assent instruments will be administered in an online call, and electronic questionnaires will be used to collect detailed information about participants’ health and language history, demographic characteristics, and attitudes toward study participation, as well as to assess the impact of RSSD on the participant’s socio-emotional well-being. The in-person assessment will include the eligibility tasks described in the previous section. Participants will also produce custom probes assessing imitative production of /ɹ/ at the single syllable level (stimulability probe [42]) and non-imitative production of /ɹ/ at the word level and sentence level.

Individuals who meet all eligibility criteria will be asked to return for an additional testing session. This session will gather information about auditory and somatosensory acuity, which we will use to address separate research questions. This session will also allow us to administer additional eligibility testing if any results from the initial testing session were inconclusive. In particular, participants who did not pass the CELF-5 screening measure will complete the full CELF-5 Core Language Index. This additional testing session will also allow for the administration of the maximum performance tasks described above to any participants who passed one but not both of the screening measures used to rule out CAS.

### Group allocation

Participants will be randomly allocated to one of two groups in a 1:1 ratio. The *in-person* group will receive visual-acoustic biofeedback treatment from a clinician in a private room in research space at Syracuse University or Montclair State University, while the *telepractice* group will receive equivalent treatment delivered via videoconferencing. As indicated above, random allocation will be stratified by both baseline accuracy and study site. To determine baseline accuracy, the stimulability probe will be rated by the clinician who administered the evaluation and a clinician at the other study site. Based on these ratings, participants will be categorized as more stimulable (both clinicians score the participant as showing > 0% accuracy in baseline stimulability probe) or less stimulable (at least one clinician scores 0% accuracy in baseline stimulability probe). The study statistician will generate confidential participant treatment assignments in batches, where each batch corresponds to a combination of site (Montclair State University versus Syracuse University) and response category (more versus less stimulable). Within each batch, half of the participants in each of the four combinations of accuracy level and site will be allocated to the in-person condition and half allocated to the online condition. To avoid a situation where study team members can predict the allocation of an upcoming participant based on their knowledge of previous allocations within the batch, batch sizes were randomly chosen from a collection of possible sizes ranging from 16 to 96 (reflecting the fact that the size of each batch needs to be a multiple of eight).

In cases where a participant drops out prior to study completion, we will invite the participant to return for a follow-up assessment after the typical duration of treatment elapses, in order to measure their outcomes in the absence of the treatment. For participants who decline to participate in this follow-up assessment, in the intention-to-treat analysis, we will generate an imputed score based on data from the other participants in the group the missing participant was assigned to. To support this imputation, participants will complete one assessment session at the midpoint of treatment (after treatment session 10). We will also conduct an adjusted per-protocol analysis, described below under *Data analysis*.

